### Sample size and statistical analysis

Assuming a type I error of 0.05, a correlation between pre and post-intervention values of the Short Physical Performance Battery (SPPB) of *r* = 0.6 and a standard deviation for the SPPB of 2.5, the required sample size to detect with a power of 90% a minimum difference of 1 point between groups in the change of SPPB score is 87 patients per group [27]. Assuming losses of 20%, the final objective of the size of each group is 109 patients, and, consequently, a total sample size will be 218 subjects. For the estimation, an ANCOVA method for the analysis of the differences has been considered. The outcome variables will be analyzed using mixed models, without missing data imputation. If the proportions of missing data are very large (more than 40%) on important variables, then trial results will be considered as hypothesis-generating results.

Baseline values will be compared by group using descriptive statistics as mean and standard deviation or median and interquartile range for quantitative variables and frequencies and percentages for categorical ones. To determine the efficacy of the intervention in the quantitative variables, such as the SPPB, we will use ANCOVA models, using post-intervention value as dependent variable, group study as the principal effect and pre-intervention value as covariate. If relevant group differences were observed at baseline, we would adjust for these variables in the model. In the case of qualitative or categorized variables (such as whether an improvement of a given magnitude between pre and post-intervention has been achieved or not), comparisons between groups will be conducted with the chi-square test or Fisher’s test, and complemented with logistic regression if additional adjustment is needed.

The level of statistical significance will be 0.05. Data will be analyzed using an intention-to-treat approach and using SPSS and R statistical software.

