### Outcome measures

#### Primary outcome

The primary outcome measure is the change in functional and cognitive status and the change of quality of life during the study period. The functional capacity of patients will be evaluated by the Short Physical Performance Battery (SPPB) (Annex 1), which combines balance, gait ability and leg strength using a single tool. The total score will range from 0 (worst) to 12 points (best). The SPPB test has been shown to be a valid instrument for screening frailty and predicting disability, institutionalization and mortality. The magnitude of meaningful change was a one-point change in the score which has clinical relevance. If the total score is less than 10, it indicates frailty and a high risk of disability and falls.

The capacity will be assessed with the Mini-Mental State Examination (MMSE) (Annex 2). This examination is composed of seven categories designed to assess specific cognitive functions: orientation to time (5 points), orientation to place (5 points), registration of three words (3 points), attention and calculation (5 points), recalling the three words (3 points), language (8 points) and constructive visual capacity (1 point).

The MMSE score ranges from zero to 30 points, and lower values indicate possible cognitive deficit. Values from 27 to 30 denote preserved cognitive functions; from 24 to 26, changes that do not suggest deficit; from 20 to 23, changes that suggest cognitive deficit. Scores from 20 to 26 represent mild cognition impairments; between 11 and 20, moderate cognition impairment; and scores under 10 represent severe cognition impairments.

Changes in quality of life will be assessed by EuroQol-5D-VAS (Annex 3). This is a generic health status questionnaire, consisting of five dimensions (mobility, self-care, usual activities, pain/ discomfort, anxiety/depression) including three responses. It also includes a visual analogue scale for recording an individual’s rating of their current health-related quality of life (scale 0 to 100).

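### Responder outcomes get an unadjusted test by default, with logistic regression added only on an undefined condition; adjusting for the baseline score would gain a little power at no cost (minor)

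*Protocol article*

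**What the plan says.** The protocol article, section Sample size and statistical analysis, treats the two kinds of outcome differently.

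- Quantitative outcomes such as the SPPB: ANCOVA of the post-intervention value, with group as the main effect and the pre-intervention value always a covariate. Other variables are added if relevant baseline differences are seen.
- Qualitative or categorised outcomes, the example being whether a patient improved by a given amount: "comparisons between groups will be conducted with the chi-square test or" Fisher's test, "complemented with logistic regression if additional adjustment is needed".

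No cut-off is fixed for the responder. The section Primary outcome states that "The magnitude of meaningful change was a one-point change in the score" of the SPPB, which runs from 0 to 12, but gives this as clinical relevance and not as a responder definition. The assessment table shows SPPB, MMSE and EuroQol all measured during admission, so a baseline score exists for each scale that might be dichotomised.

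**The concern.** Whether a patient gains a given number of points depends on where that patient starts. High starters tend to fall back, low starters tend to rise, and the scale stops at 0 and 12. Baseline therefore predicts response, and a model that includes it should detect a treatment effect more often than a crude comparison of proportions. The plan takes this gain for the continuous score and leaves it aside for the dichotomised one.

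The conditional clause adds a second, smaller problem. Logistic regression comes in as a complement, on a condition that is not defined. A crude and an adjusted p-value can then both exist for one outcome, with nothing to say which is decisive. At stake are some precision and a clear rule for reading the result, not the validity of the planned test.

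**Working it through.** **Inputs from the protocol** (Sample size and statistical analysis): significance level 0.05; for the correlation, "a correlation between pre and post-intervention values of the Short Physical Performance Battery (SPPB) of *r* = 0.6"; SPPB SD 2.5; power 90% for a 1-point difference between the arms in SPPB change; and, as the outcome of that calculation, that the requirement "is 87 patients per group". Sidedness is not stated; I take the test as two-sided.

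**Step 1: reproduce the plan's figure.** The ANCOVA residual SD is 2.5 × √(1 − 0.6²) = 2.0. Then n per group = 2 × (1.96 + 1.2816)² × 2.0² / 1² = 84.1, so 85, or 86 with the noncentral t. That agrees with 87 within rounding; power at 87 is 0.91. Dividing by 0.8 for 20% losses gives 87 / 0.8 = 108.75, so 109 per group and 218 in total, as stated. An unadjusted two-sided comparison of change scores has SD 2.5 × √(2 × 0.4) = 2.236 and needs 2 × 10.51 × 5.0 = 105.1, so 106 per group. The stated size thus fits an analysis that uses baseline as a covariate, which is the method the text names.

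**Step 2: power for a responder outcome.** Trials were simulated with 87 per group, bivariate normal scores with the plan's SD, correlation and effect, rounded and clipped to 0–12. Each was analysed by uncorrected chi-square and by logistic regression on group and baseline SPPB (Wald test). Two inputs are assumptions that the documents do not give: the baseline mean (6 in this table) and the mean change in the control group. Each row has 2,500 runs, so the simulation error of a single power figure near 60% is √(0.6 × 0.4 / 2500), about 1 percentage point.

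| Responder definition | Control change | Chi-square | Logistic with baseline | Gain (points) |
|---|---|---|---|---|
| Gain ≥ 1 point | 0 | 68.1% | 72.0% | 3.8 |
| | 1 | 60.2% | 66.1% | 5.8 |
| | 2 | 49.5% | 54.7% | 5.2 |
| Gain ≥ 2 points | 0 | 60.2% | 65.8% | 5.6 |
| | 1 | 66.4% | 69.4% | 3.0 |
| | 2 | 55.9% | 64.0% | 8.1 |

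Extending the baseline mean to 4, 6 or 8 with the same control changes and cut-offs makes 3 × 3 × 2 = 18 settings. Adjustment gained power in all 18, by about 2 to 11 percentage points.

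**Step 3: type I error.** With no treatment effect, baseline mean 6, control change 1 and 6,000 runs per cut-off:

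| Responder definition | Chi-square | Logistic with baseline | Smaller p-value of the two |
|---|---|---|---|
| Gain ≥ 1 point | 5.9% | 5.4% | 7.4% |
| Gain ≥ 2 points | 5.3% | 5.1% | 7.0% |

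Each test alone stays close to 5%. Only the habit of taking the better of the two moves it to about 7%.

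**The case against.** The strongest case against raising this is that it concerns an analysis the trial has not listed. The responder appears only in a parenthesis. The primary and secondary outcome lists contain none, and the outcomes that are categorical as listed, such as delirium or readmission, have no baseline score and rightly stay with chi-square or Fisher. This stands, and it is why the point is minor.

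It can also be said that covariates for a supportive model belong in the SAP. That would hold if the protocol were silent. It is not: it names an unadjusted test as the default and a condition for adjusting.

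A reader might infer more than the text supports:

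- *The crude test is biased or invalid.* It is not. Regression to the mean and the scale limits act alike in both arms, and the simulated level is near 5%.
- *The baseline score is thrown away.* A pre-to-post responder uses it in its definition. What is unused is baseline as a covariate.
- *The plan allows the better p-value to be picked.* The default test is fixed, and logistic regression complements it without replacing it. The 7% shows what an undefined rule could cost; it does not describe a stated procedure. The rule tied to observed baseline differences is written for the ANCOVA.
- *The missing adjustment explains the gap to ANCOVA.* In the setting with a gain of at least 1 point and a control change of 1, ANCOVA on the score has about 90% power against 60% for chi-square, but adjustment recovers only 5.8 of those points. The rest comes from dichotomising, which this point does not challenge.

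**Conclusion.** The point holds in a limited form. For a categorised outcome built from a scale measured at baseline, the stated default is valid but less efficient than it need be, and the clause on adjustment leaves open when it applies and which result counts.

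The size is about 2 to 11 percentage points of power at 87 per group. It rests on the plan's SD, correlation and 1-point effect, on bivariate normal scores rounded to the scale, and on assumed baseline means of 4 to 8, control changes of 0 to 2 and cut-offs of 1 or 2 points. The direction was the same in every setting tried; the exact gain depends on those assumptions. The sample size and the baseline-adjusted analysis of the continuous SPPB are untouched.

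**What to change.** For any categorised outcome derived from a scale measured at baseline, state that the main analysis is logistic regression with group and that scale's baseline score. Report the adjusted odds ratio together with a standardised risk difference, because the odds ratio is conditional on the covariate and harder to read clinically. Delete the conditional clause for these outcomes, so that one result is decisive in advance. Keep chi-square or Fisher for outcomes that have no baseline score or very few events. No covariate beyond the baseline score is needed to settle this point; the calculations tested none.

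The cost is one sentence in the analysis section, with no new data and no change in sample size. It should be settled before outcome data are compared by group.

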### Methods for further analysis

Subgroup analyses will be performed to understand whether exercise is more or less effective according to age, type of surgery, comorbidity or hospital stay. These subgroup analyses will follow the same plan as the primary analysis, as well as their interaction with the experimental condition.

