**Methods/design:**

This study is a randomized clinical trial, simple blinded, conducted in the Department of Surgery of a tertiary public hospital in Navarra (Hospital Universitario de Navarra), Spain. Patients >  = 70 years old undergoing urgent abdominal surgery who meet inclusion criteria will be randomly assigned to the intervention or control group. The intervention will consist of a multicomponent physical training programme, which will include progressive and supervised endurance, resistance and balance training for 4 weeks, twice weekly sessions with a total of 8 sessions, and the group control will receive the usual care. The primary outcome measure is the change in functional (SPPB) and cognitive status (Mini-Mental State Examination) and the change of quality of life (EuroQol-5D-VAS) during the study period. The secondary outcomes are postoperative complications, length of stay, delirium, mortality, use of health resources, functional status (Barthel Index and handgrip strength tests), cost per quality-adjusted life year and mininutritional assessment. The data for both the intervention group and the control group will be obtained at four different times: the initial visit during hospital admission and at months 1, 3 and 6 months after hospital discharge.

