## Methods/design

### Study design

This study is a parallel group, two-arm, superiority randomized trial with 1:1 allocation ratio, is monocentric and is conducted in the Department of Surgery of a tertiary public hospital in Navarra (Hospital Universitario de Navarra), Spain. Patients undergoing urgent abdominal surgery who meet inclusion criteria will be randomly assigned to the intervention or control group.

Patient recruitment will begin in 4 days after the surgical procedure, and these patients will be identified through the list of patients admitted to the hospital and assigned to the Department of General Surgery. Prior to randomization, the investigators will review the contraindications to participate in the exercise programme and will provide general information about the study. After signing an informed consent form, the subjects will be chosen randomly. 

Randomization will be performed by applying http://www.randomizer.org/. The doctor who decides the inclusion in the intervention or control group will not be the attending physician. Patients will be informed of the random inclusion in one of the groups.

The information in both groups is obtained in four different stages: the initial visit and at months 1, 3 and 6 after hospital discharge.

The protocol employs relevant standard protocol items for clinical trials according to the SPIRIT 2013 statement [29] and follows the CONSORT statement [30] for transparent reporting.

The trial is registered at ClinicalTrials.gov, identifier NCT05290532.

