#### Secondary outcome measure

Postoperative complications: Clavien Dindo (Annex 4) and Comprehensive Complication Index (Annex 5)Length of stayDelirium: Confusion Assessment Method (CAM) (Annex 6)Mortality: number of days alive after admission to the hospitalUse of health resources: new admission to the hospital, admission to nursing homes and visits to the general practitionerFunctional status: Barthel index (Annex 7)Cost per quality-adjusted life year: both direct and indirect study participant costsMininutritional Assessment short form (MNA) (Annex 8)Handgrip strength test

Surgeons and physiotherapists will help participants to fill in the questionnaires. The information in both groups is obtained in a face-to-face consultation in four different stages: the initial visit and at months 1, 3 and 6 after hospital discharge. The questionnaires and tests are easy to perform, and the studio staff is qualified to perform them in a homogeneous way. The scales that we used to evaluate functional capacity [32, 33], mental state [34], quality of life [35] and nutritional status [36] have been validated for use in Spain.

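### Hospital stay is a planned subgroup factor, yet it is completed after randomisation and is itself a secondary outcome, so treatment effects within stay groups are open to bias if allocation affects stay

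*Protocol article*

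**What the plan says.** Under Methods for further analysis, the protocol article sets out to learn "whether exercise is more or less effective according to age, type of surgery, comorbidity or hospital stay". On method it says: "These subgroup analyses will follow the same plan as the primary analysis, as well as their interaction with the experimental condition". Hospital stay has no definition and no cut-off there.

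The abstract (Methods/design) also treats stay as a result of the trial: "The secondary outcomes are postoperative complications, length of stay, delirium, mortality, use of health resources". The list under Secondary outcome measure repeats it.

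On timing, Study design says "Patient recruitment will begin in 4 days after the surgical procedure". Candidates are "identified through the list of patients admitted to the hospital and assigned to the Department of General Surgery", and "After signing an informed consent form, the subjects will be chosen randomly". The abstract places the initial visit during the admission and counts the later visits from discharge.

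**The concern.** Age, type of surgery and comorbidity can all be fixed before allocation. Total hospital stay cannot, because patients are randomised on the ward and the discharge date comes later. The same variable also appears as an outcome, so the plan allows that the arms may differ on it.

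If the programme shortens stay for some patients, the short-stay group in the exercise arm gains patients who would have stayed long under usual care. Those patients are likely to recover less well. Within the short-stay group, and likewise within the long-stay group, the two arms then hold different kinds of patients. The estimated SPPB difference mixes the effect of exercise with that imbalance. At stake is the reading of the treatment effect in patients with short and long stays.

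**Working it through.** **1. Is stay known at allocation?** Recruitment starts from day 4 after surgery, among inpatients, and randomisation follows consent. No section says that allocation waits for discharge, and none defines hospital stay as the time before randomisation. Total stay is therefore a post-randomisation quantity.

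**2. Can allocation change it?** The article leaves this open. The Background places the programme in the first month after surgery, so training could overlap the admission, but no start date relative to discharge is given. Under Randomization and blinding, assessors are blinded, while patients and training staff are not. The allocating doctor is not the attending physician, but nothing says that those who decide discharge are unaware of the arm.

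**3. The plan's own figures, for scale.** From Sample size and statistical analysis: SD 2.5, pre-post correlation 0.6, difference 1 point, alpha 0.05 (two-sided assumed), power 90%, ANCOVA.
- Residual SD = 2.5 × √(1 − 0.6²) = 2.0.
- n per group = 2 × (1.960 + 1.282)² × 2.0² / 1² ≈ 84.1, so 85. This is within 2 of the stated 87.
- 87 / 0.80 = 108.75, so 109 per group and 218 in total, as stated.
- SE of the effect in a half-sample subgroup at 87 per arm = 2.0 × √(2/43.5) ≈ 0.43.
- SE of the interaction = 2.0 × √(4/43.5) ≈ 0.61.

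**4. Size of the bias.** The documents give no distribution of stay, no effect of arm on stay and no link between stay and SPPB. All of these are assumed:
- mean stay 12 days, SD 4, split at 12 days;
- correlation ρ of stay with function of -0.3 or -0.6;
- stay shortened by 0, 1 or 2 days in the exercise arm;
- no true effect on SPPB, so any difference is false.

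Without baseline adjustment there is a closed form. With d = days shortened / 4, and φ and Φ the normal density and distribution function:
- short stay: 2.5 × |ρ| × [φ(d)/Φ(d) − φ(0)/0.5]
- long stay: −2.5 × |ρ| × [φ(d)/(1 − Φ(d)) − φ(0)/0.5]

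For 2 days and ρ = -0.6 (d = 0.5):
- short: 1.5 × (0.509 − 0.798) = -0.43
- long: −1.5 × (1.141 − 0.798) = -0.52

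The plan uses ANCOVA with the pre-intervention value as covariate. Adding a baseline correlated 0.6 with the post value and simulating 4 million patients per scenario gives:

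| Correlation | Stay shortened by | Short stay | Long stay | Long minus short |
|---|---|---|---|---|
| either | 0 days | 0.00 | 0.00 | 0.00 |
| -0.3 | 1 day | -0.07 | -0.08 | -0.01 |
| -0.3 | 2 days | -0.14 | -0.17 | -0.02 |
| -0.6 | 1 day | -0.16 | -0.18 | -0.02 |
| -0.6 | 2 days | -0.30 | -0.36 | -0.06 |

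**5. Sensitivity to the set-up.** A second simulation gave every patient a true effect of 1 point. It correlated longer stay with poorer recovery after baseline adjustment, at 0.3 to 0.5.
- Stay shortened by 0.2 SD, median split: both strata show 0.92 to 0.93 at correlation 0.3, and 0.87 at 0.5.
- Stay shortened by 0.5 SD, median split: 0.81 in both strata at 0.3, and 0.68 in both at 0.5.
- Stay shortened by 0.5 SD, split at the 75th percentile: 0.86 and 0.78 (short and long stay) at 0.3, and 0.77 and 0.61 at 0.5. The false interaction is about 0.08 to 0.16 points.
- Stay unaffected by arm: about 1.00 in both strata.

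**The case against.** The strongest reply is that bias needs allocation to move the discharge date, and the article never says that it does. Twice-weekly sessions on weight machines and a cycle ergometer over 4 weeks would fit training after discharge. If all training starts then, only unblinded discharge decisions could shift stay, and the bias could be small or nil. This stands, and it is why the point is openness to bias.

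Three stronger readings are tempting, and the documents do not support them.
- **That the subgroup effects are certainly biased because stay is an outcome.** Listing a variable as an outcome shows that the team will compare it between arms. It does not show that the arms differ on it.
- **That the false effect reaches half of the 1-point target.** That comes from the unadjusted comparison (-0.52). With the planned baseline adjustment, the same extreme scenario gives about a third (-0.36).
- **That the interaction test would mislead on who benefits.** The error is similar in both strata, so it mostly cancels in the interaction: 0.01 to 0.06 points, or up to 0.16 with an uneven split, against an SE of about 0.61.

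One could also read hospital stay as the stay before randomisation, which would remove the problem. No section says so. The missing cut-off may be left to a fuller document and is not the complaint. The choice of variable is stated in the article itself.

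**Conclusion.** The point holds as a design weakness in a secondary analysis. Total stay is settled after randomisation and is a listed outcome, so comparisons within stay groups lack the protection of randomisation. Bias follows if allocation alters stay and stay shares causes with recovery.

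Under the assumptions in step 4, the planned ANCOVA would show a false difference of about -0.07 to -0.36 SPPB points in both strata. The sensitivity runs, with other correlations and cut-offs, go up to 0.39 points too low. These sizes rest on assumed values for stay and are smaller than the standard error of a half-sample subgroup (about 0.43). The case for change is that the comparison is unsound in principle and almost free to correct. The primary comparison and the sample size of 218 are unaffected.

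**What to change.** In Methods for further analysis, delete hospital stay from the subgroup factors and keep length of stay only as a secondary outcome. If a marker of severity or slow recovery is wanted, use a quantity fixed before allocation:
- **Baseline SPPB.** It is already scheduled during the admission; state that it is measured before allocation.
- **Days from surgery to randomisation,** if both dates are recorded. This interval is not among the listed assessments.

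Complication grade at randomisation is less secure, because the schedule lists Clavien-Dindo during admission and at 1 month, with no reading tied to allocation. If hospital stay was meant as stay before randomisation, the text should say so.

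Keep the arm-by-factor interaction for the remaining factors. The cost is one line of wording. Deletion or baseline SPPB needs no new data and no change in sample size. The article describes recruitment as still open, so the change can be made before the analysis and entered in the trial registry.
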